### Statistics

#### Power Calculations

To compute sample size, the proportion of patients free from cholelithiasis was assumed to be 100% 5 years after gastrectomy plus prophylactic cholecystectomy. It is known from the current literature that the cumulative incidence of cholelitiasis 5 years after gastrectomy is around 15–25% while in the general population 5 years cumulative incidence is around 5% [1-4]. The 5-yr cumulative incidence of cholelithiasis after cholecystectomy is known to be null. Hence we assumed a 5 years cumulative incidence of 20% in patients undergoing gastrectomy alone and of 0% in patients undergoing gastrectomy + cholecystectomy.

Gastrectomy with concomitant cholecystectomy was assumed to increase cholelithiasis-free survival from 80% to 100%. Assuming a constant accrual rate and an accrual time of 2 years, a minimum follow-up period of 3 years, an overall survival probability of 50% at 5 years, 122 patients (61 in the control group and 61 in the cholecystectomy group) are necessary to ensure an 80% power with an alpha of 5%, when using a two-sided log-rank test.

Assuming a 50% drop-out rate during a 3 years follow-up allows to account for both cancer mortality and follow-up loss. These assumptions were based on the fact that competing events (deaths) will be substantial while patients lost from follow-up will be few. In a GIRCG series of 1032 patients undergoing gastrectomy plus lymphadenectomy 3 years disease-related survival was 59% (95% CI 41–60%), while no patient was lost to follow-up in the first 3 years after gastrectomy[15]. Therefore, to be conservative, we assumed a 50% loss during a follow-up period of three years, to account for both cancer mortality and loss to follow-up.

The statistical power sample calculation was carried out using PASS 2005 (Power Analysis and Sample Size, within the statistical package "NCSS 2004 and PASS 2005")[16] (see additional file 1).

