#### Primary aims of the study

The aim of the study is to compare the results of gastrectomy plus prophylactic cholecystectomy versus gastrectomy only in patients undergoing gastric cancer surgery with a curative intent, in terms of morbidity, mortality, operation time, hospital stay, postoperative pain, return to normal activity, quality of life, and development of biliary symptoms after 5 years from surgery.

The primary aims of our study will be:

A) To evaluate whether patients who had not a prophylactic cholecystectomy and developed cholelithiasis will eventually suffer from symptoms related to their gallstones and will need another surgical intervention 5 years after gastrectomy

B) To evaluate the incidence of cholelithiasis in patients who have undegone gastric surgery

C) To evaluate whether prophylactic cholecystectomy increases complications rate, operative time and postoperative stay.

The onset of any other complications will be recorded intraoperatively, postoperatively, at discharge, 4-months after surgery. Subsequently, visits will be scheduled every 6-months in first two years after surgery, and yearly thereafter till completion of the 5-year follow-up.

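### The stated 80% power covers only stone onset, a contrast whose direction is known beforehand; it supports neither aim A nor aim C, and aim A as worded is not a comparison of randomised arms

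*Protocol article*

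**What the plan says.** **Power Calculations.** The only sample-size calculation concerns cholelithiasis: "Hence we assumed a 5 years cumulative incidence of 20% in patients undergoing gastrectomy alone and of 0% in patients undergoing gastrectomy + cholecystectomy". The effect to be detected is put this way: "Gastrectomy with concomitant cholecystectomy was assumed to increase cholelithiasis-free survival from 80% to 100" per cent. The zero is treated as established: "The 5-yr cumulative incidence of cholelithiasis after cholecystectomy is known to be null". The result is that "122 patients (61 in the control group and 61 in the cholecystectomy group) are necessary" for 80% power with a two-sided 5% log-rank test.

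**Tests.** Kaplan-Meier curves for onset of cholelithiasis are compared by the log-rank test. This is the contrast that was powered.

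**Primary aims of the study.** An opening sentence promises a comparison of the two treatments on several outcomes, including morbidity and biliary symptoms at 5 years. Three primary aims follow:

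- A: whether patients who kept the gallbladder and then developed stones "will eventually suffer from symptoms related to their gallstones and will need another surgical intervention 5 years after gastrectomy".
- B: the incidence of cholelithiasis after gastric surgery.
- C: whether adding cholecystectomy raises the complication rate, operative time and postoperative stay.

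No power or precision is given for A or C.

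**The concern.** The Introduction says that many patients with stones after gastrectomy never have symptoms or need surgery, and it gives the expected benefit as avoided reintervention. By that reasoning, stones seen on ultrasound do not decide whether prophylactic removal is worthwhile. Symptoms and reoperations avoided, weighed against added morbidity, do.

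The one powered test cannot address this. If the cholecystectomy arm cannot form gallbladder stones, the null hypothesis of equal stone onset is false by construction, and rejecting it shows only that a removed gallbladder forms no stones. A significant log-rank result could nevertheless be read as support for routine cholecystectomy.

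Aim A does not fill the gap as worded. It conditions on an event after randomisation (stone formation) in one arm only. Randomisation then gives no protection, and biliary events or reoperations in the other arm do not enter the aim.

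**Working it through.** **Inputs (Power Calculations).** Control stone incidence 20% at 5 years; cholecystectomy arm 0%; 61 per arm; two-sided 5%; power 80%. Accrual and follow-up: "Assuming a constant accrual rate and an accrual time of 2 years, a minimum follow-up period of 3 years, an overall survival probability of 50" per cent at 5 years. A second attrition figure follows: "Assuming a 50% drop-out rate during a 3 years follow-up allows to account for both cancer mortality and follow-up loss". The two differ, so both are carried below.

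**1. Hazards (exponential).** Stones: λ = −ln(0.8)/5 = 0.0446 per year. Death or loss: μ = ln 2/5 = 0.1386 (50% at 5 years) or ln 2/3 = 0.2310 (50% at 3 years). Let s = λ + μ.

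**2. Probability of an observed stone in a control patient**, with follow-up uniform between 3 and 5 years:

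p = (λ/s) × [1 − (e^(−3s) − e^(−5s))/(2s)] = 0.1259 (50% at 5 years) or 0.1075 (50% at 3 years).

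**3. Reproducing 122.** Freedman's formula at hazard ratio 0 needs (1.960 + 0.842)² = 7.85 events. With no events in the treated arm, the mean event probability is p/2, so N = 7.85/(0.1259/2) = 124.7, within 3% of 122. Power at 122 is 79.1%. With 50% loss at 3 years, N = 146. So 122 follows from the stone contrast with the 5-year attrition figure.

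**4. What is fixed and what is not.** In simulated trials (10,000 runs per setting, N = 122, treated arm at zero) none went in the opposite direction. The proportion reaching significance varied with control incidence:

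| Control 5-year incidence | 50% loss at 5 y | 50% loss at 3 y |
|---|---|---|
| 25% | 99% | 97% |
| 20% | 95% | 87% |
| 15% | 80% | 68% |
| 5% | 10% | 6% |

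**5. Information for aim A.** Expected control patients with stones: 61 × 0.1259 = 7.7 or 61 × 0.1075 = 6.6. If every survivor is followed for 5 years, p = (λ/s)(1 − e^(−5s)) = 0.1461 or 0.1211, giving 8.9 or 7.4. The exact (Clopper-Pearson) 95% CI for 2 symptomatic of 7 is 3.7% to 71.0%; for 2 of 9 it is 2.8% to 60.0%.

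**6. Aim A as a between-arm question.** The documents give no symptomatic fraction, so 10% to 50% of stones is assumed, with no events in the cholecystectomy arm. Expected symptomatic controls run from 6.6 × 0.1 = 0.7 to 8.9 × 0.5 = 4.5. With k events, all in controls and with equal risk sets, the log-rank z is (k/2)/√(k/4) = √k, so k = 4 (z = 2.0) is needed for nominal significance. The binomial chance of at least 4 of 61 runs from 0.4% (fraction 10%, 50% loss at 3 years) to 66% (fraction 50%, 5 years for all, 50% loss at 5 years). As a cross-check with no deaths at all, Fisher's test at 61 per arm has power of 0.1%, 8% and 58% for 2%, 5% and 10% versus 0%.

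**7. Aim B.** With complete follow-up, 12 of 61 gives an exact 95% CI of 10.6% to 31.8%. The 80% power does not set this width.

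**8. Aim C.** Base complication rates are assumed, since none is given. Two-proportion test, 61 per arm, for a rise of 10 percentage points; half-width = 1.96 × √{[p₁(1 − p₁) + p₂(1 − p₂)]/61}:

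| Rates | Power | 95% CI half-width (points) | n per arm for 80% |
|---|---|---|---|
| 10% vs 20% | 34% | 12.5 | 199 |
| 20% vs 30% | 25% | 15.3 | 294 |
| 30% vs 40% | 21% | 16.8 | 356 |

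**The case against.** The strongest reply is that the protocol misstates no figure here. The 122 reproduces, and the 80% is tied in the text to cholelithiasis-free survival; nowhere is it claimed for symptoms or complications. An article may leave precision for other endpoints to the full protocol or to its additional file, which is not shown. This stands as far as it goes: the point concerns which contrast drives the sample size and how aim A is worded. It is not an arithmetic error.

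Several stronger readings are tempting, and the documents do not support them:

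- *The result is fixed in advance.* Only the direction is. Significance depends on control incidence, as the simulations show.
- *The power covers none of the primary aims.* Aim B shares the powered endpoint, and the Tests section evaluates differences in incidence by the same log-rank test.
- *The protocol ignores biliary events after cholecystectomy.* That is true of aim A's wording only. The opening sentence of the aims names a between-arm comparison of biliary symptoms, and ultrasound, hepatic tests and visits to 5 years are not restricted to one arm.
- *There must be a single primary endpoint.* Making symptomatic disease the only primary endpoint at 122 patients would give a poorly powered primary and push the harm comparison aside. That is a debatable trade-off, not a correction the documents require.
- *A family-wise error rate can be attached to the three aims.* Aims A and B, as worded, are not between-arm tests, and a false null on stones adds no type I error, so no such figure is sound.

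**Conclusion.** The concern holds in limited form. The only powered test compares stone onset in a direction the protocol already takes as known, so it cannot show that prophylactic cholecystectomy benefits patients. Its 80% reaches aim B only through the shared endpoint and supports neither aim A nor aim C. Aim A's restriction to control patients with stones is at odds with the between-arm comparison of biliary symptoms announced in the same section.

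The count of about 7 to 9 control patients with stones rests on the plan's own inputs and exponential times. The CI of 4% to 71%, the 0.4% to 66% chance of reaching four symptomatic events, and the 21% to 34% power for complications rest on assumed symptomatic fractions and base rates. The exact values would move with those assumptions. Any estimate for symptoms would remain very imprecise across the range examined.

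**What to change.** 1. Reword aim A to compare symptomatic biliary disease or biliary re-intervention within 5 years between all randomised patients by assigned arm. Report a difference in cumulative incidence with 95% CI, alongside the aim C harm comparison.
2. Report stone incidence as a control-arm estimate with 95% CI (aim B). Do not present the log-rank test on stones as evidence of benefit.
3. State in Power Calculations that the 80% applies to ultrasound-detected stones only, and give the expected precision for aims A and C at 122 patients, with the assumed rates named.

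Cost: no added patients, procedures or visits, since aim A already needs these events and follow-up to 5 years is planned. The wording of the primary aims changes in a registered, ethics-approved trial, so an amendment is needed, and the stated power will look less favourable.

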Patient discharge will be based on good medical practice criteria: 1) apyrexia 2) absence of diseases requiring hospitalisation 3) light meals tolerance 4) return of bowel function 5) patient's compliance. A routine ultrasonography of hepathobiliary region will be scheduled after 4 and every 6 months for the first two years and yearly for the rest of the follow-up (at least 5 years) to assess possible cholelithiasis development. Routine blood check with specific hepatic tests will be collected with the same schedule. Routine oncologic follow-up in an outpatient setting are also added according to current protocols.

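### The power calculation states two attrition assumptions that do not agree; at the stated 3-year minimum follow-up, 122 patients matches the milder one, not the 50% loss by 3 years that the text calls conservative

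*Protocol article*

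**What the plan says.** All of the sample-size reasoning is in the protocol article, section Power Calculations.

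- Effect: "Gastrectomy with concomitant cholecystectomy was assumed to increase cholelithiasis-free survival from 80% to 100"%, meaning a 5-year cumulative incidence of 20% after gastrectomy alone and 0% with cholecystectomy.
- Time frame: "Assuming a constant accrual rate and an accrual time of 2 years, a minimum follow-up period of 3 years".
- Attrition, first statement: "an overall survival probability of 50% at 5 years, 122 patients", 61 per group.
- Test and target: these patients "are necessary to ensure an 80% power with an alpha of 5%, when using a two-sided log-rank test".
- Attrition, second statement, in the next paragraph: "to be conservative, we assumed a 50% loss during a follow-up period of three years", meant to cover cancer deaths and loss to follow-up together. The same paragraph expects few losses other than death.
- Supporting evidence: in a series of 1032 patients, "3 years disease-related survival was 59% (95% CI 41–60"%), with nobody lost to follow-up in the first 3 years.

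Elsewhere the planned follow-up is longer. Data Collection schedules ultrasound "yearly for the rest of the follow-up (at least 5 years"), and Primary aims of the study plans visits until 5 years are completed and sets its aims at 5 years.

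**The concern.** A single sample size is presented as resting on two attrition assumptions, and a reader cannot tell which one produced it. If 122 comes from the milder assumption, the statement that the design allows conservatively for half the patients being lost by year 3 is not true of the number printed.

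Two further figures weaken the justification. The interval around the cited 59% does not fit the sample size given. The calculation also uses 3 to 5 years of follow-up per patient, while the schedule promises at least 5.

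At stake is whether the stated 80% power can be relied on, and under which attrition and follow-up. The expected number of gallstone events is small and all of them fall in one arm, so modest changes in attrition or follow-up move the result.

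**Working it through.** **Inputs from Power Calculations.** Two-sided alpha 5%, power 80%, log-rank test; gallstone-free at 5 years 80% v 100%; uniform accrual over 2 years; minimum follow-up 3 years, so 3 to 5 years per patient; 61 per arm.

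**Assumptions added here.** Constant gallstone hazard in controls, λ = −ln(0.8)/5 = 0.0446 per year. Constant attrition hazard μ, except where a plateau is tested.

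**1. Do the two attrition inputs agree?**
- 50% survival at 5 years: survival at 3 years = 0.5^(3/5) = 0.66, so 34% lost by year 3.
- 50% loss by 3 years: remaining at 5 years = 0.5^(5/3) = 0.315.
- Cited 59% at 3 years: at 5 years = 0.59^(5/3) = 0.415.

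To move from 66% to 50% at year 3 through non-death loss would need 1 − 0.50/0.66 = 24% lost, although such losses are said to be few.

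**2. Events needed.** Freedman's formula with the hazard ratio tending to 0: d = (1.96 + 0.842)² = 7.85, all in the control arm.

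**3. Probability of a control event.** For follow-up t, p(t) = λ/(λ+μ) × [1 − exp(−(λ+μ)t)], averaged over t from 3 to 5 years. Then N = 2 × 7.85 / p. Formula power at 122 = Φ(√(61p) − 1.96).

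| Attrition (3–5 years of follow-up) | μ | p | N for 80% | Events at 61 controls | Formula power at 122 |
|---|---|---|---|---|---|
| 50% survival at 5 years | 0.139 | 0.1259 | 125 | 7.68 | 79% |
| 59% at 3 years (cited series) | 0.176 | 0.1179 | 133 | 7.19 | 77% |
| 50% loss by 3 years | 0.231 | 0.1075 | 146 | 6.56 | 73% |

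The first row reproduces the protocol's 122; a Lachin–Foulkes-type formula gives 121 to 123. The third row does not: Lachin–Foulkes gives 142 to 144. If half are lost by year 3 and nobody afterwards, p = 0.1100 and N is still about 143 (formula power 74%).

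**4. Same sums at the follow-up the schedule plans.**

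| Attrition | Follow-up | p | N for 80% | Formula power at 122 |
|---|---|---|---|---|
| 50% survival at 5 years | exactly 5 years | 0.1461 | 107 | 85% |
| 50% loss by 3 years | exactly 5 years | 0.1211 | 130 | 78% |
| 50% loss by 3 years | 5–7 years | 0.1305 | 120 | 81% |

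**5. The printed interval.** For 59% of 1032 with complete 3-year follow-up: 0.59 ± 1.96 × √(0.59 × 0.41/1032) = 0.59 ± 1.96 × 0.0153 = 56.0% to 62.0%. A 19-point width would correspond to about 103 patients (1.96² × 0.59 × 0.41 / 0.095² = 103).

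**6. Few events.** Expected control events at 61 patients run from 6.6 to 8.9 for the two protocol inputs across steps 3 and 4. Fisher's exact test with 61 per arm gives p = 0.119 for 4 v 0, 0.057 for 5 v 0 and 0.027 for 6 v 0. The binomial chance of at least 6 control events is 80% (50% survival at 5 years) or 65% (50% loss by 3 years) at 3–5 years of follow-up, and 90% or 76% with 5 years for everyone. Simulated power of the ordinary asymptotic log-rank test at 122 and 3–5 years is about 94–95% or 88%.

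**The case against.** The strongest reply is that 122 does fit the harsher input at the follow-up actually scheduled. With 50% lost by year 3 and 5 to 7 years of follow-up, N is about 120 and formula power 81%. This stands, so it would be wrong to say that 122 matches only the milder input. The mismatch is tied to the 3-year minimum that Power Calculations itself states ("a minimum follow-up period of 3 years").

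Second, the two inputs conflict only under a roughly constant hazard. Half lost by year 3 with a plateau to year 5 satisfies both statements. That is true as logic, but N at 3–5 years is then still about 143, so the recalculation is unaffected.

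Third, as an assumption, 50% loss by year 3 is harsher than the 41% implied by the cited series, so the word conservative suits it. That is fair; the trouble is that this assumption does not yield 122 at the stated follow-up. A reader might go further and use the printed lower limit of 41% to argue that even 50% loss is too mild. That does not work, because the limit belongs to an interval that is itself wrong.

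Fourth, a reader might infer that nobody would be at risk at 5 years and the 5-year aims could not be estimated. The documents do not support this: ultrasound and visits are scheduled to at least 5 years, and nothing says the final analysis stops at a 3-year minimum.

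Fifth, a reader might infer that the trial is underpowered. For the planned asymptotic log-rank test that is not shown; simulated power is about 88% even under the harsher input. The low figure of 65% appears only with an exact criterion at 3–5 years.

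Finally, the additional file with the software calculation is not shown and may state which input was entered. It could settle the source of 122 but would not make the two published statements agree.

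**Conclusion.** The point holds as an error of statement. At the accrual and follow-up given in Power Calculations, 122 patients for 80% power follows from 50% survival at 5 years (N about 125) and not from 50% loss by 3 years (N about 143 to 146, some 17% to 20% above 122). The input that yields 122 is also more favourable than the cited 59% at 3 years (N about 133). The description of 122 as allowing conservatively for 50% loss by year 3 is therefore wrong at the stated follow-up, by about 6 points of formula power (79% v 73%).

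At the planned 5 years for everyone the gap largely closes: about 78% under the harsher input and 85% under the milder. The printed 41–60% interval cannot be right for 59% of 1032 patients with no loss by 3 years.

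These figures rest on a constant gallstone hazard, a constant attrition hazard (or the plateau variant), uniform accrual and a formula that is rough at 6 to 9 events. They are no evidence that the planned log-rank test falls below 80% power.

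**What to change.** In Power Calculations:

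1. State one all-cause attrition assumption, with its values at 3 and 5 years, and drop the other.
2. Base the calculation and the final analysis on the follow-up of at least 5 years that the schedule already plans.
3. Restate power for 122 patients on that basis. By the formula above and exactly 5 years of follow-up, this is about 78% if half are lost by year 3 and about 85% if survival is 50% at 5 years; with 5 to 7 years of follow-up and the harsher input it is about 81%.
4. Correct the interval for the cited 59%, which should be about 56–62% for 1032 patients with complete 3-year follow-up.
5. In Tests, add an exact or permutation log-rank p-value beside the planned one, because only about 6 to 9 events are expected, all in one arm.

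The cost is a recalculation and a corrected paragraph, with no extra patients and no added visits. The downside is a somewhat lower stated power, both from the single attrition input if the harsher one is kept and from the exact test (76% to 90% at 5 years by the chance of at least 6 control events).

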#### Tests

To evaluate significance of differences between the two groups, chi-squared and Fisher's exact test will be used as appropriated for categorical variables, and the non-parametric Mann-Whitney U-test for continuous variables. To evaluate differences in the incidence of cholelithiasis, Kaplan-Meier survival curves will be computed considering as endpoint the onset of cholelithiasis itself. Survival curves will be compared by log-rank test and multivariable analysis will be accomplished by the Cox regression model. Significance level will be set at 5%. The statistical analysis will be carried out using the Statistical Package for the Social Sciences (SPSS version 13; SPSS Inc. Chicago, Illinois, USA).

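### Kaplan-Meier with stone onset as the only endpoint will overstate the incidence of cholelithiasis asked for in aim B, because many patients are expected to die stone-free

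*Protocol article*

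**What the plan says.** The Tests section of the protocol article fixes the method. "To evaluate differences in the incidence of cholelithiasis", it says, "Kaplan-Meier survival curves will be computed considering as endpoint the onset of cholelithiasis itself"; the curves are then compared by log-rank test and modelled by Cox regression. No competing-risk estimator is named, and no censoring rule is written out.

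Aim B, under Primary aims of the study, is "To evaluate the incidence of cholelithiasis in patients who have undegone gastric surgery".

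Power Calculations makes three relevant statements:
- On deaths, it says that "competing events (deaths) will be substantial while patients lost from follow-up will be few".
- On survival, it takes "an overall survival probability of 50% at 5 years" and, separately, "we assumed a 50% loss during a follow-up period of three years, to account for both cancer mortality and loss to follow-up". It also cites an earlier series in which "3 years disease-related survival was 59" per cent.
- On stones, "Hence we assumed a 5 years cumulative incidence of 20% in patients undergoing gastrectomy alone", against 0% after added cholecystectomy.

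**The concern.** A patient who dies of gastric cancer without stones can no longer develop them. If that patient is censored, Kaplan-Meier treats the future stone risk as still open and represented by those who remain alive. 1-KM therefore describes a hypothetical population in which death does not occur. It does not give the proportion of operated patients who develop stones, which is the ordinary meaning of incidence in aim B.

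The protocol names the competing event when it sets the sample size but makes no use of it when it chooses the estimator. At stake is the absolute stone burden in the control arm. The other arm is assumed to have none, so any overstatement in the control arm passes in full into the risk difference and makes the preventable burden look larger than it is.

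**Working it through.** **Are deaths censored?** This is an inference, with two supports in Power Calculations.

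1. The section assumes 80% and 100% free of cholelithiasis alongside 50% overall survival at 5 years. If deaths counted as events, neither figure could exceed 50%.
2. The planned size is approximately recovered when deaths are treated as censoring. The stone hazard is l = -ln(0.80)/5 = 0.0446 per year. The death hazard is m = ln 2/5 = 0.1386 per year. Let h = l + m = 0.1833. With uniform accrual over 2 years and 3 to 5 years of follow-up, the control-arm event probability is (l/h) × [1 - (e^(-3h) - e^(-5h))/(2h)] = 0.2435 × [1 - (0.5771 - 0.4000)/0.3665] = 0.1259. The Freedman formula at hazard ratio 0 requires (1.960 + 0.842)² = 7.85 events. The mean event probability over both arms is 0.1259/2 = 0.0630, so N is about 124.7 against the stated 122. The match is close but not exact: rounding up per arm gives 126, and a Lakatos calculation gives 115. With 50% lost by 3 years instead, the Freedman figure is 146.

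**Size if 20% is the 1-KM value at 5 years.** Under constant, independent hazards:

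- 1-KM(5) = 1 - e^(-5l) = 0.200
- actual cumulative incidence: CIF(5) = (l/h) × (1 - e^(-5h))

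| Mortality input | m per year | CIF(5) | 1-KM / CIF | Excess, points |
|---|---|---|---|---|
| 50% alive at 5 years | ln 2/5 = 0.1386 | 0.2435 × 0.600 = 14.6% | 1.37 | 5.4 |
| 59% alive at 3 years | -ln(0.59)/3 = 0.1759 | 0.2024 × 0.668 = 13.5% | 1.48 | 6.5 |
| 50% gone by 3 years, all by death | ln 2/3 = 0.2310 | 0.1619 × 0.748 = 12.1% | 1.65 | 7.9 |

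**Size if 20% is the actual cumulative incidence.** Solving CIF(5) = 0.20 for l and putting it into 1 - e^(-5l) gives a 1-KM reading of 27.2% with 50% alive at 5 years (ratio 1.36). With 50% dead by 3 years it gives 32.5% (ratio 1.63).

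**Sensitivity.**
- Over the 15–25% range that the protocol cites, on either reading, the relative excess is 35–37% with 50% alive at 5 years and 61–66% with 50% dead by 3 years.
- Weibull hazards (shape 0.5 to 2 for stones, 0.7 to 1.5 for death) give ratios from 1.16 to 2.10. The low end has early stones, late deaths and 50% alive at 5 years. The high end has late stones and 50% gone by 3 years.
- If stones are found only at scheduled scans (assumed at 4, 10, 16, 22, 36, 48 and 60 months), simulated ratios are 1.44 and 1.80 for the first and third mortality inputs.

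**Direction.** In any one data set, the cumulative incidence estimate weights each new stone by the proportion alive and stone-free. 1-KM weights it by the larger stone-free proportion that ignores deaths. When deaths precede some stones, 1-KM is the higher of the two whatever the hazard shapes.

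**The case against.** Several points on the other side stand.

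- **The group comparison is sound.** A reader might infer that the log-rank test, and with it the basis of the sample size, is invalid. It is not. With deaths censored, log-rank and Cox compare cause-specific stone hazards, which is a legitimate question.
- **Symptoms and re-intervention.** A reader might carry the same bias over to aim A. Tests assigns Kaplan-Meier only to the onset of cholelithiasis; the general rule there for categorical variables is chi-squared or Fisher's exact test. The documents do not support the extension.
- **The size is not a forecast.** A reader might take one third to two thirds as the expected overstatement. The protocol states no hazard shapes. The 3-year 50% is a deliberately conservative allowance that mixes death with loss to follow-up, and the 59% is disease-related rather than overall survival. The only direct overall-survival assumption is 50% at 5 years.
- **The meaning of 20% is unknown.** The protocol calls it a cumulative incidence taken from literature. Whether the sources censored deaths cannot be told from the document, so 14.6% is conditional and not an established true value.
- **Risk in the absence of death has some use.** The Introduction frames one argument for prophylaxis around surviving patients. That justifies showing the Kaplan-Meier curve under a correct label, but it does not make the curve the incidence among all operated patients.

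The lack of a written censoring rule is also a fair point, but the protocol's own survival figures leave little room for another reading.

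**Conclusion.** The point holds for the absolute estimate under aim B. As written, the plan uses 1-KM with stone-free deaths censored by inference, in a population where the protocol itself expects substantial competing mortality. Read as incidence in operated patients, that estimate and the between-arm difference in 5-year risk will be too high.

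The best-supported illustration is 20% against 14.6%, an excess of 5.4 points or 37% in relative terms. It assumes constant, independent hazards, 50% alive at 5 years, and 20% as the 1-KM value. The 12.1% figure is an outer case that counts the entire conservative loss allowance as death. Other hazard shapes move the relative excess between about 16% and 110%. Only its upward direction is secure.

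This is a stated method that does not match a stated aim, rather than a detail left to an analysis plan.

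**What to change.** In Tests, state that for aim B the incidence of cholelithiasis will be estimated by the Aalen-Johansen cumulative incidence function, with death before stones as a competing event. Report 5-year values per arm and their difference with 95% confidence intervals. Censor only true losses to follow-up and administrative end of follow-up.

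Keep the log-rank test and Cox model, labelled as cause-specific comparisons. The Kaplan-Meier curve may stay if labelled as risk in the hypothetical absence of death. Use the same cumulative incidence estimator for symptoms and re-intervention only if they are analysed as time-to-event outcomes.

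The cost is analysis work, software that computes cumulative incidence, and a date of death for each patient who dies. The protocol does not state explicitly that this date is recorded, but it should be obtainable, since oncologic follow-up is planned and mortality is a listed outcome. The reported incidence will be lower than the Kaplan-Meier figure. The design and the log-rank test on which the trial was sized are unaffected.

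### If the cholecystectomy arm has no stones, as the protocol expects, a treatment term in the planned Cox model has no finite hazard ratio and its Wald interval and p-value are uninformative

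*Protocol article*

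**What the plan says.** Protocol article, Statistics, Tests: the paragraph sets out to evaluate differences in the incidence of cholelithiasis. It plans Kaplan-Meier curves with onset of cholelithiasis as the endpoint and a log-rank comparison, then states that "multivariable analysis will be accomplished by the Cox regression model". It lists no covariates and does not say how the model coefficients will be tested. The significance level is 5% and the software is SPSS version 13.

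Protocol article, Statistics, Power Calculations: "we assumed a 5 years cumulative incidence of 20% in patients undergoing gastrectomy alone and of 0% in patients undergoing gastrectomy + cholecystectomy". The zero is also given as established fact: "The 5-yr cumulative incidence of cholelithiasis after cholecystectomy is known to be null". On this basis the article concludes that "122 patients (61 in the control group and 61 in the cholecystectomy group) are necessary". The target behind that number is 80% power for the log-rank test, two-sided at the 5% level. The inputs include "Assuming a constant accrual rate and an accrual time of 2 years, a minimum follow-up period of 3 years" and 50% overall survival at 5 years. A second statement allows for 50% loss, from deaths and drop-out together, within 3 years.

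**The concern.** A Cox model estimates a finite hazard ratio between two arms only if both contribute events. The protocol names a Cox model for an endpoint that it says cannot occur in one arm. With treatment in the model, the expected data are exactly those on which ordinary Cox estimation breaks down. No choice of adjustment covariates cures this.

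At stake is a confusing report. A convincing log-rank result could stand beside an adjusted hazard ratio printed as practically zero, with an unbounded interval and a p-value near 1, from the same patients. A second issue is that a multivariable model would rest on very few events, all from one arm.

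**Working it through.** **1. Reproducing the sample size.** The assumed hazard ratio is ln(1)/ln(0.8) = 0. Freedman's log-rank formula then needs (1.960 + 0.842)² = 7.85 events. Control-arm event hazard: λ = −ln(0.8)/5 = 0.0446 per year. Death hazard for 50% survival at 5 years: μ = ln(2)/5 = 0.1386. Sum: 0.1833. The probability of an observed stone by time t is (λ/(λ+μ))·(1 − e^(−(λ+μ)t)). Averaged over 3 to 5 years of follow-up (uniform 2-year accrual) this is 0.1259. Hence N = 2 × 7.85/0.1259 = 124.7, within 3% of the stated 122. Freedman power at 61 per arm is 79.1%.

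**2. Expected events among 61 controls.**

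| Assumption | P(event) | Events |
|---|---|---|
| 50% loss by 3 years, follow-up 3–5 years | 0.1075 | 6.6 |
| 50% mortality by 5 years, follow-up 3–5 years | 0.1259 | 7.7 |
| 50% mortality by 5 years, all followed 5 years | (0.0446/0.1833) × (1 − 0.4) = 0.146 | 8.9 |

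The cholecystectomy arm contributes 0 throughout.

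**3. The Cox treatment term with one empty arm.** Let θ be the hazard ratio and d the number of events, all in controls. With roughly equal risk sets, the partial likelihood is proportional to (1 + θ)^(−d). It increases all the way to θ = 0, so the log hazard ratio β has no finite maximum. The standard error from the information is (1 + θ)/√(dθ), which grows faster than |β|, so the Wald ratio tends to 0.

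One trial simulated from the protocol's inputs (4 events against 0) shows this:

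| Iterations | β | SE (fitted) | SE (formula, d = 4) | Wald p |
|---|---|---|---|---|
| 5 | −6.2 | 11 | 11.1 | 0.58 |
| 10 | −11.2 | 135 | 135 | 0.93 |
| 15 | −16.2 | 1,648 | 1,647 | 0.99 |
| 20 | −21.2 | 20,080 | 20,067 | 0.999 |

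The output reflects the stopping point and nothing about the patients.

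**4. What remains informative.** Under the same equal-risk-set approximation:

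- Log-rank (score) chi-square = (d/2)²/(d/4) = d. With d = 4 this is 4, above 1.96² = 3.84, so it is significant where every Wald p-value in the table is not.
- Likelihood-ratio chi-square = 2d·ln(2) = 1.386d. With d = 4 it is 5.5.
- Profile-likelihood upper 95% limit: solve 2d·ln(1 + θ) = 3.84. For d = 7.7, θ = e^(3.84/15.4) − 1 = 0.28. For d = 6.6 it is 0.34 and for d = 8.9 it is 0.24.

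In about 1,900 simulated trials under each of the first two loss assumptions in step 2, fitted with treatment and one binary covariate, the Wald test never rejected. The likelihood-ratio test rejected in about 99% and the score test in 92–96%. The median profile upper limit was about 0.27–0.31. The unadjusted log-rank test had simulated power of 95% (50% mortality by 5 years) and 88% (50% loss by 3 years).

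**5. Other covariates.** A binary covariate other than treatment was estimable: mean log hazard ratio about 0.73 against a true 0.69, median SE about 0.73. That SE gives a 95% interval from the estimate divided by 4.2 to the estimate times 4.2 (e^(1.96 × 0.73) = 4.2).

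**6. Dependence on exactly zero events.** If the true hazard ratio were 0.05 (my assumption), the chance of no events in the cholecystectomy arm would be about 67–71%. At 0.10 it would be about 43–49%.

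**The case against.** The Tests section does not say that treatment is in the model. A model of risk factors alone is possible: the Introduction names extent of gastrectomy and lymphadenectomy as possible determinants, both are recorded under Data Collection, and one primary aim concerns the incidence of stones after gastric surgery. Covariate lists and the handling of sparse data are commonly left to an analysis plan. No Wald test is named either, and the treatment effect can be tested in the same model by likelihood ratio. Finally, the breakdown needs exactly zero observed events.

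Most of this stands, and it makes the point conditional. It does not remove it. The sentence on the Cox model continues one about comparing the two arms' curves, so a treatment term is the natural reading. The protocol itself presents zero events as known. An analysis plan could choose covariates, but it could not make the ordinary treatment estimate finite on such data.

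A reader might infer that following the plan must yield a non-significant treatment result, with some particular p-value. The documents do not support that: they name no Wald test, and any specific coefficient, standard error or p-value reflects an iteration limit. A reader might also infer that risk-factor estimates would be artefacts. They would not; they are estimable but imprecise.

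**Conclusion.** The concern holds conditionally. With treatment in the Cox model and no stones in the cholecystectomy arm, there is no finite maximum-likelihood hazard ratio, and the Wald interval and p-value carry no information and can conflict with the log-rank test. Any covariate estimates would rest on about 7 to 9 events, assuming exponential hazards and the protocol's incidence, survival and loss figures.

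It would be wrong to conclude that the trial cannot compare its arms. The log-rank test, on which it is powered, works with an empty arm, and the stated sample size is reproduced closely. The defect is confined to an additional model and is worth correcting mainly because the correction is cheap.

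**What to change.** Amend the Tests section to say that:

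- the log-rank test is the treatment comparison for cholelithiasis, and the effect is reported as the difference in 5-year cumulative incidence. Its confidence interval must suit zero events in one arm and allow for censoring, for example by combining separate limits for each arm so that the empty arm is not treated as known without error;
- any adjusted hazard ratio is accompanied by a likelihood-ratio test and a profile-likelihood limit, or comes from a Firth-penalised Cox fit, and Wald inference is not used for it;
- any risk-factor model is restricted to the gastrectomy-only arm, with very few covariates named in advance, and is labelled exploratory.

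Treatment need not be dropped from an adjusted model if one of these methods is used. The cost is about one added sentence and software beyond standard SPSS Cox output. Sample size and trial conduct do not change.
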